### Sub-group analyses

Additional analysis of secondary outcomes will include only participants who will be considered as active participants and another analysis of those who will be considered non-active participants. The text messaging intervention requires active participation of study participants to be effective. Participants who respond to the weekly text messages > 80% of the time will be considered as active respondents; those who respond ≤ 80% of the time will be considered as non-active respondents. The 80% cutoff may be revised as appropriate. Participants who never respond to the text message, for whatever reason, will be included in the usual care group. The sample size will be too small to perform further sub-group analysis.

The statistician under the guidance of a senior biostatistician (LT), will conduct all analyses while blinded to study assignment. Stata 14 (StataCorp, College Station, TX, USA) will be used for analysis.

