### Mobile phone text messaging

Consented new mothers will register their phone numbers into an automated text message (SMS) software (provided by WelTel.org). The first SMS will be sent within the first week following delivery. Every Monday morning, a text message will be sent to women in the intervention group encouraging them to exclusively breastfeed and inquire if they have any problems breastfeeding their infants. Participants will be asked to respond by text within 48 h, indicating that they either do not have a problem or they have a problem and require help. Participants may also use the free ‘call back’ function to request a call from the nurse for complex issues or if cost or literacy is a problem. The research nurse will review all the responses and then follow-up and provide triage to any participants who indicate a problem or call participants who fail to respond within 48 h. To preserve confidentiality, the content of the text messages will not be related to the woman’s HIV status. Participants will be briefly trained on use of the phone and the text messaging protocol.

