### Secondary outcomes

We will follow the Consolidated Standards of Reporting Trials (CONSORT) extension for reporting pilot trials [40]. We will use the intention-to-treat principle for secondary outcome analysis, where all participants randomized will be considered per group assignment. In this analysis, we will impute missing outcome data using both the best-case and worst-case scenario. For adherence outcomes, missing data at study visits will be considered as “adherent” and “non-adherent,” respectively. For breastfeeding outcome, missing data at study visits will be considered as “stopped breastfeeding” and “still breastfeeding.” The study is not adequately powered to test intervention effects and these will be of secondary interest to assess potential trends. Logistic regression models will be built for binary outcomes. For timed endpoints, the cumulative proportions of women stopping exclusively breastfeeding and cumulative proportions of those stopping any breastfeeding, we will use the Kaplan–Meier survival analysis followed by multivariable Cox proportional hazards model to adjust for possible baseline imbalances. We will report odds ratios and hazard ratios (95% CI) as initial estimates of effect. Table 1 provides a summary of methods of analysis for each variable. Separately, we will conduct sub-analysis to assess subgroup effects, a summary of this analysis follows below.

**Table 1 Tab1:** Variables, measures, and methods of analysis

Variable/Outcome	Type	Hypothesis	Outcome measure	Method of analysis
l. Primary				
a. Participants recruited	Count		Percentage recruited	Descriptive statistics
b. Participants consenting	Count		Percentage consenting	Descriptive statistics
c. Completeness of evaluation of outcomes	Count		Percentage with complete outcome evaluation	Descriptive statistics
d. Cumulative breastfeeding adherence at six months	Binary		Percentage adherence in the last 24 h and 1 week	Descriptive statistics
2. Secondary				
a. Adherence to exclusive breastfeeding	Binary	SMS + motivational interview leads to better adherence to breastfeeding than usual care	Percentage adherence in the last 24 h and 1 week	Logistic regression
b. Time to stopping breastfeeding	Time-to-event	SMS + motivational interview prolongs time to stopping breastfeeding than usual care	Reporting of complete cessation of breastfeeding	Kaplan–Meier survival analysis

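### The additional analysis of secondary outcomes counts intervention women who never reply to texts as usual care, and splits women by a reply rate that exists only in the intervention arm

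*Protocol article*

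**What the plan says.** The Secondary outcomes part of the analysis plan adopts intention-to-treat, under which "all participants randomized will be considered per group assignment". It then announces a separate sub-analysis, described under Sub-group analyses:

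- "Additional analysis of secondary outcomes will include only participants who will be considered as active participants", with a second analysis for the non-active.
- The split rests on replies: "Participants who respond to the weekly text messages > 80% of the time will be considered as active respondents". Women at or below 80% are non-active.
- On the threshold: "The 80% cutoff may be revised as appropriate".
- On women with no replies at all: "Participants who never respond to the text message, for whatever reason, will be included in the usual care group".
- The statistician "will conduct all analyses while blinded to study assignment".

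Under Mobile phone text messaging, texts go to one arm only: "Every Monday morning, a text message will be sent to women in the intervention group". The research nurse will also "call participants who fail to respond within 48 h". The Motivational interviewing section schedules interviews in weeks 2, 6 and 10 and does not make them depend on replying.

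**The concern.** Replying is observed after randomisation and can be observed in only one arm. Using it to decide which arm a woman counts in, or which women enter a comparison, gives up the balance that randomisation provides. Women who disengage from texting may well be those who stop breastfeeding. Moving them would then remove poor outcomes from the intervention group and add them to usual care, which produces a difference even if the intervention does nothing.

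The rule does not work as an as-treated definition either. A woman who never texts back is still sent the weekly message, called by the nurse and scheduled for interviews. The rule applies whatever the cause of non-reply, so it could also catch a woman who uses the free call-back function, which is offered where cost or literacy is a problem, and who never sends a text.

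The split by reply rate has related weaknesses. Usual-care women have no reply rate, so neither sub-group has a matching control group, and no comparator is named. Never-repliers also meet the definition of non-active, so two rules apply to them. The threshold is open to change, with no rule or time limit stated.

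**Working it through.** **Inputs from the protocol.** Recruitment is five per week for 12 weeks: 5 × 12 = 60, which matches the stated sample size. Allocation is 1:1, so about 30 per arm. No power calculation is stated, so there is none to reproduce.

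**Assumed inputs.** The documents give no reply rates and no adherence by reply status. As a background rate I take 50% adherent, borrowed from the earlier cohort cited in the Background, where 50% switched to formula at about four months. Using it for 24-week adherence is an assumption. The number of never-repliers and their adherence are varied.

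**Re-allocation with no true effect.** Each arm has 30 × 0.5 = 15 adherent women. Move m women with adherence p:

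- intervention = (15 − m·p)/(30 − m)
- usual care = (15 + m·p)/(30 + m)

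| Never-repliers moved | Their adherence | Intervention | Usual care | Spurious difference |
|---|---|---|---|---|
| 0 | – | 15/30 = 50.0% | 15/30 = 50.0% | 0 |
| 1 | 20% | 14.8/29 = 51.0% | 15.2/31 = 49.0% | +2.0 points |
| 3 | 20% | 14.4/27 = 53.3% | 15.6/33 = 47.3% | +6.1 points |
| 6 | 20% | 13.8/24 = 57.5% | 16.2/36 = 45.0% | +12.5 points |
| 6 | 0% | 15/24 = 62.5% | 15/36 = 41.7% | +20.8 points |
| 6 | 50% | 12/24 = 50.0% | 18/36 = 50.0% | 0 |
| 6 | 70% | 10.8/24 = 45.0% | 19.2/36 = 53.3% | −8.3 points |

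With q = m/30, the difference simplifies to 2q(0.5 − p)/(1 − q²). For six movers at 20%: 2 × 0.2 × 0.3/0.96 = 0.125. The sign therefore depends only on whether never-repliers do worse or better than their arm as a whole.

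**Re-allocation with a true effect.** Take 70% versus 50% adherent (21/30 versus 15/30), a true difference of 20 points, and six never-repliers.

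- If they gain nothing (50% adherent): (21 − 3)/24 = 75.0% versus (15 + 3)/36 = 50.0%, or 25 points.
- If they gain fully (70% adherent): (21 − 4.2)/24 = 70.0% versus (15 + 4.2)/36 = 53.3%, or 16.7 points.

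The rule can distort a real effect in either direction.

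**Active and non-active sub-groups with no true effect.** Suppose 60% of the arm (18 women) are active and 65% of them adherent, which is 11.7 women. The other 12 then contain 15 − 11.7 = 3.3 adherent women, or 27.5%. Set against usual care at 50%, the active group shows +15 points and the non-active group −22.5. Usual care as the comparator is itself an assumption.

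**The case against.** The strongest defence is about scope. Intention-to-treat is the stated analysis of the secondary outcomes, and the reply-based analyses are introduced as separate and additional. The trial is a 60-woman pilot with descriptive feasibility outcomes, and effects are said to be of secondary interest. This stands, and it lowers the severity. What remains is that the re-allocation sentence carries no limit to this section, and that it is a poor rule even inside it.

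A reader might infer several stronger points that the documents do not support:

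- *The intention-to-treat analysis, or the 70% adherence criterion for feasibility, is itself corrupted.* Nothing says that either uses the re-allocated groups.
- *The estimates are always biased towards benefit.* The direction is expected for re-allocation and for the active group, but it is not certain. It is nil or reversed if never-repliers do as well or better, and the non-active comparison is expected to err against benefit.
- *The bias is large.* With phone training and a nurse call after each missed reply, women with no replies at all may be few, and one such woman gives only about +2 points.
- *These estimates will set the main trial's sample size.* The Sample size section refers to initial estimates of effect. The Secondary outcomes text uses that phrase for its own odds and hazard ratios, before the sub-analysis is introduced.
- *A woman who stops breastfeeding early can never be active.* With a fixed 24 messages, more than 80% means at least 20 replies (0.8 × 24 = 19.2). No such denominator is stated, and a woman who only stops exclusive breastfeeding stays in follow-up.
- *The cut-off will be chosen after seeing results.* The wording permits this but does not say it, and the Ethical aspects section requires protocol modifications to be notified.
- *Analyst blinding must fail.* Having reply data identifies the arm, so unmasking is likely. Study staff could, however, supply coded groups prepared in advance.

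**Conclusion.** The point holds for the additional analysis of the secondary outcomes. Counting never-repliers as usual care departs from analysis by assigned group and misdescribes what those women were offered. The reply-rate split gives sub-groups with no randomised comparator.

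If never-repliers do worse than their arm, apparent benefit is inflated. The protocol's premise that texting needs active participation to work points that way. The size cannot be fixed from the documents. Under the stated assumptions it runs from 0 with no never-repliers to about +21 points with six at 0% adherence, and to about −8 if six do better at 70%.

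The main intention-to-treat analysis is unaffected provided the rule is confined to this section, which the text should say but does not. Severity is should-fix: the analysis is secondary and exploratory, but the rule is wrong as written and easily removed.

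**What to change.** 1. Delete the sentence that places never-repliers in usual care. State that every woman stays in her randomised arm in all between-arm comparisons.
2. Report the number of never-repliers, and outcomes by active or non-active status, descriptively within the intervention arm as an engagement result, with no comparison to usual care.
3. Fix the 80% cut-off before any outcome data are seen, and remove the sentence that allows it to be revised.
4. Run the intention-to-treat analysis first under masked arm codes, and state that the engagement analyses may reveal the arm.

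The cost is the rewording of one paragraph. The Trial status section says recruitment has not begun, so no data are affected. What is lost is a responder-versus-control estimate that could not be interpreted as an effect of the intervention.

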## Ethical aspects

The study will be conducted according to the ethical guidelines and principles of the International Declaration of Helsinki, South African Guidelines for Good Clinical Practice, and the Medical Research Council Ethical Guidelines for Research [41, 42]. Participants will provide written informed consent. Participants will receive R150 (~US $10) for their participation time, transport, lunch on study visit days, and any other study-related costs. There are no anticipated physical risks involved in participating in the study; however, participants will be insured by Stellenbosch University’s research policy in the event of some form of physical injury occurring as a direct result of taking part in this study. The Stellenbosch University Human Research Ethics Committee approved the study protocol (reference no. N16/09/11). This pilot trial will not have a Data and Safety Monitoring Board. The study will not have a codebreaking rule for randomization as the study is unblinded, except for data analysts. All investigators declare no competing interests. If there are any protocol modifications, the ethics committee, trial registry, and trial participants will be informed. Study results will be presented in aggregate format in technical reports and journal publications.

## Discussion

The pilot trial evaluates the feasibility of conducting a larger trial on communication and support approaches that may improve adherence to exclusive and continued breastfeeding by HIV-infected women. Several clinical trials on mobile phone text messaging showed improved treatment adherence for chronic medication, including diabetes, HIV, and tuberculosis. Text messaging and motivational interviewing will allow participants to access personalized adherence advice and support. Text messaging is simple and popular among participants and healthcare providers and this may maximize its use in real practice settings. Additionally, our study is unique in that it tests the ability to combine a number of approaches to influence behavior change.

The study will be conducted in a setting where adherence to breastfeeding is poor. This risks finding larger differences between the intervention and control groups than what could be found in settings with better baseline adherence to breastfeeding. However, we assume the intervention would show a similar trend in direction of effect, in settings with better adherence to breastfeeding. Another disadvantage of our study design is that both healthcare providers and the population whose behavior we are attempting to change (including those in the usual standard of care group) are sensitized to the potential benefits of the intervention during enrolment. We will record the frequency with which participants attend the primary healthcare clinics during follow in order to identify any dose-response relationships between interventions and behavior change.

The design and analysis plan will allow us to assess the effect of the intervention on secondary outcomes. The results of this pilot trial will inform further development of a larger trial on use of mobile phone text messaging plus motivational interviewing to improve breastfeeding practices of HIV-infected women in resource-limited settings. While our measure of behavior change is based on mothers’ self-report rather than more objective measures that accurately predict infant feeding behavior, it is a widely used approach for measuring change in infant feeding practices.

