## Study interventions

All women and their infants, irrespective of their study assignments, will receive health services and treatment according to the respective provincial guidelines applicable in the sector during the study. No deviation from existing guidelines will be caused by taking part in this study. Participants will be evaluated soon after giving birth and post delivery until cessation of breastfeeding or until end of the study. Children will be tested for HIV infection at time points already in routine practice (i.e. at birth and ten weeks). We will extract information on the children’s HIV status from the clinical and laboratory records.

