### Motivational interviewing

In addition to text messaging, women will have individual motivational interviews post delivery at weeks 2, 6, and 10. Study visits will be in line with the Expanded Program of Immunization routine schedule to maximize participation [37]. We will train the research nurse in motivational interviewing techniques, which include reflective listening and expression of acceptance and affirmation. These techniques will enable the research nurse to understand participant’s frame of reference, reinforce participant’s own self-motivational statements, monitor the readiness to change, and affirm the participant’s freedom of choice. Advice will be given with participant’s permission, and when given, the participant will make her own choice. The research nurse will apply these techniques considering the participant’s readiness to change. The interviews will be recorded.

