### Secondary endpoints

Secondary outcomes include number of participants who are exclusively breastfeeding 24 weeks post delivery and number of participants who are breastfeeding. This will be assessed using a questionnaire of food items given to the baby in the last 24 h and one week preceding inquiry. Participants will be considered either “adherent” to exclusive breastfeeding if babies receive only breastmilk and no other liquids or solids based foods or “non-adherent” if other foods are given. Breastfeeding will be assessed by self-report of women who report breastfeeding in addition to giving other foods. Study outcomes will be evaluated at weeks 2, 6, 10, and 24.

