## Data collection and management

Data collection tools will include a baseline questionnaire and a follow-up questionnaire (at weeks 2, 6, 10, and 24 post randomization). Our questionnaires were developed using a validated WHO infant feeding questionnaire [39]. The questionnaires will be used in English and will be administered by a research nurse or counsellor fluent in the participant’s language. In instances where study participants speak only local languages, the researcher nurse will translate questions directly. We will inquire about feeding practices during the previous 24 h and during the prior week. Study follow-up, SMS messages, and responses will be recorded on a study log weekly. Telephone communications with participants in the usual care group not receiving text messages will be recorded in a similar study log. Clinic records will be reviewed for clinically relevant data. Study follow-up will continue until complete cessation of breastfeeding or until end of study.

To maintain participant confidentiality, only a coded number will identify all questionnaires, reports, and other records. A unique patient identification number will be used to link participant-specific data. All paper records will be kept in a locked file cabinet at the research site and at the Centre for Evidence Based Health Care, Stellenbosch University. Access will be limited to research staff. Electronic files will be password-protected. Clinical information will not be released without written permission of the participant, except if required by the ethics review committee. Participant names will be stored separately. No reports will link individual names with person level data. The research nurse or counsellor will receive training prior to beginning of the trial. A standard operations manual will be available to staff for reference on operational details.

Data will be transcribed from the paper format into an electronic database. We will check data to ensure that entered values are acceptable, required fields are completed, and items are consistent with other related items in the database. We will verify with source documents for any discrepant entries. A record of the database update will be kept, identifying information about the person who made the changes, date, changed values, and comments.

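### The clinic-attendance dose-response is tied to a follow-up that ends when breastfeeding stops, so a simple visit count would track the outcome even with no effect

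*Protocol article*

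**What the plan says.** The Discussion of the protocol article states an analytic intention: "We will record the frequency with which participants attend the primary healthcare clinics during follow in order to identify any dose-response relationships". The sentence goes on to name these as "dose-response relationships between interventions and behavior change". It gives no model, and Table 1 has no row for this analysis.

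Two other sections fix how long a woman is observed. Study interventions has evaluation running "post delivery until cessation of breastfeeding or until end of the study". Data collection and management repeats this: "Study follow-up will continue until complete cessation of breastfeeding or until end of study".

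The time-to-event outcome in Table 1, time to stopping breastfeeding, is measured by "Reporting of complete cessation of breastfeeding". The assessment schedule is: "Study outcomes will be evaluated at weeks 2, 6, 10, and 24". In the intervention arm, "women will have individual motivational interviews post delivery at weeks 2, 6, and 10"; these come on top of the weekly text messages.

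**The concern.** On the plain reading of these sections, the event that is the outcome also closes the period in which attendance is recorded. A woman who breastfeeds to week 24 has 24 weeks in which to attend; a woman who stops at week 8 has 8. Longer breastfeeding then produces more recorded visits, whatever visits do to breastfeeding. This is the familiar immortal-time problem: the exposure is partly a function of the outcome.

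The dose is also imprecise. The intervention is the texts and the interviews, whereas women in both arms attend the clinic, and illness or motivation may drive attendance as well. An association could therefore be read as support for the intervention, and carried into the design of the larger trial, when it only reflects how visits were counted.

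**Working it through.** The article gives no figure for this analysis, so there is none to reproduce. The check asks how large an association appears when there is none.

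**Inputs from the article**
- Sample size 60: 5 per week × 12 weeks (Primary endpoints).
- Maximum follow-up 24 weeks.
- In the earlier cohort, 50% switched to formula at about four months (Background). I read this as a median of 17.3 weeks.

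**Assumptions not in the article**
- Exponential cessation times.
- Poisson attendance at the same rate for every woman, 1/8 to 1/2 visits per week (0.1 to 0.5 in the rank-correlation runs), independent of cessation.
- Two-sided 5% tests.

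**Arithmetic check at 1/4 visit per week**
- Hazard λ = ln 2 / 17.3 = 0.0401 per week.
- Still breastfeeding at week 24: S = exp(−24λ) = 0.382.
- Mean time followed among women who stop before week 24: 1/λ − 24·S/(1 − S) = 24.96 − 24 × 0.382/0.618 ≈ 10.1 weeks.
- Expected visits: 24 × 0.25 = 6.0 in women still breastfeeding, against 10.1 × 0.25 = 2.5 in women who stopped.

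The gap of 3.5 visits comes wholly from time observed.

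**Null simulation, n = 60, logistic regression of any breastfeeding at week 24 on attendance (1,000 replicates per rate)**

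| Visits per week | Count to cessation: OR per visit | p<0.05 | Fixed 0–24 weeks: OR per visit | p<0.05 | Visits ÷ time followed: p<0.05 |
|---|---|---|---|---|---|
| 1/8 | 2.04 | 97% | 1.00 | 5% | 4% |
| 1/4 | 1.79 | 100% | 1.00 | 4% | 3% |
| 1/2 | 1.55 | 100% | 0.99 | 4% | 3% |

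Across the separate runs and tests made, the fixed window gave about 4–6%.

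**Other null settings, n = 60 unless stated**
- Count against duration of any breastfeeding: mean Spearman rho 0.60, 0.76 and 0.84 at 0.1, 0.25 and 0.5 visits per week; significant in about 100% of trials.
- Cox model with total visits as a fixed covariate, 0.25 visits per week: hazard ratio about 0.58 per visit, significant in 100%.
- Only the scheduled visits (weeks 2, 6, 10, 24), each attended with probability 80%: 3.2 against 1.6 visits, rho 0.80, significant in about 100%.
- 70% still breastfeeding at week 24 (the article's adherence target, applied here to any breastfeeding): rho 0.44–0.64, significant in 95–100%.
- One arm only, n = 30: significant against duration in 70–100%.
- Exclusive breastfeeding: rho 0.31–0.60; significant in 69–100% against duration and 28–93% for week-24 status. It is weaker because follow-up ends at complete cessation, not at loss of exclusivity.
- Visits divided by time followed, against duration: rho about 0.05–0.3, significant in about 20–50% in the base case and 13–69% over the wider set of scenarios.
- Week-10 landmark Cox model: about 3–6%.

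**The case against.** A reader might infer that the planned analysis will yield a false positive as it stands, that this would be used to justify the larger trial, and that the aim should be deleted. The article does not support that much.

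- The sentence commits only to recording attendance and gives a purpose. No model, exposure definition or outcome is fixed, and a journal article may leave these to a fuller plan. This stands, and it makes the point conditional. What remains is that the windows the article does state run to cessation.
- Frequency may mean attendances per unit time. In the logistic model of week-24 status that brings the error rate to about 3–4%, so the large figures belong to a count. A rate is still inflated against duration, so this is a partial answer.
- Clinic records are to be reviewed with no stated end date, so attendance might be captured after cessation. That is possible, but the Discussion ties the count to follow-up, and two sections end follow-up at cessation.
- Behavior change may mean exclusive breastfeeding, where the artefact is weaker. This stands.
- Interviews take place at visits aligned with the immunization schedule, and usual-care counselling is given by primary healthcare staff. Attendance is therefore a partial proxy for contact and is not irrelevant. This also stands.
- The article calls intervention effects secondary and underpowered, and no feasibility criterion uses a dose-response. That a biased result would be cited for the larger trial is conjecture.

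**Conclusion.** The point holds in conditional form. As stated, the time available to accrue attendances depends on the outcome. If attendance is counted to cessation, a dose-response with any-breastfeeding status or duration is close to certain under no effect: odds ratio about 1.5–2.0 per visit and p<0.05 in 97–100% of trials, against about 4–6% with a common 24-week window. These sizes rest on exponential cessation with a median of 17.3 weeks and on assumed attendance rates. The direction does not depend on them, and the artefact stayed strong for any breastfeeding when 70% were assumed still breastfeeding at week 24. It is smaller for exclusive breastfeeding and for a rate. The consequence is confined to an exploratory analysis; the feasibility criteria and the randomised comparisons are untouched.

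**What to change.** State that clinic attendance will be counted from the clinic records over the same fixed window, such as weeks 0–24, for every woman whether or not she has stopped breastfeeding. A landmark analysis or a time-varying exposure would also serve; dividing by time followed is not enough on its own. Report attendance by randomised arm. Label any dose-response as exploratory and observational, and say that attendance is only a partial proxy for texts and interviews received. The aim need not be deleted once the window is fixed.

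The cost is a sentence or two of wording and some extra record extraction for women who have stopped. Clinic records are already to be reviewed, and the Trial status section says recruitment has not begun.
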